#### Design

There will be three sub-studies to address Aim 2 as follows: Study 2.1, a cross-sectional study of 30–40 adults to determine validity of data collection from different types of smartphones; Study 2.2, a prospective cohort study of 50–100 adults ≥ 50 years old to assess usability and reliability, and Study 2.3, a prospective cohort study of ∼1,000 adults ≥ 50 years old to assess validity against cognitive measures. The methods to addresses Aim 2 are summarised in Fig. 4. The TapTalk test protocol on a smartphone will be based upon the findings in Study 1 and comprise around three to five of the most discriminating hand and speech-like movements, aiming for test duration of approximately 2–3 min. The TapTalk protocol may be further refined after studies 2.1 and 2.2, depending on user feedback and results.

**Fig. 4 Fig4:**

Development of smartphone application and assessment of usability and validity

#### Participants and settings

##### Study 2.1

We will undertake a cross-sectional validation study of 30–40 participants who will be recruited from staff and students at the University of Tasmania. They will be invited to attend the research centre and use their own mobile phone to video record a member of the research team (who acts as a ‘dummy’ participant) as they perform a series of finger tapping tests whilst wearing Polhemus movement sensors (as the ‘gold standard’ motor data benchmark). The Polhemus electromagnetic tracking system delivers six degrees of freedom including the position (i.e., X, Y and Z coordinates of a space) and orientation (i.e., yaw, pitch and roll), of each object with a 60 Hz sample frequency. Compared to commonly used camera-based tracking systems, the Polhemus technology allow us to collect continuous and non-interrupted data without the issue of light-of-sight occlusions. This technology has been increasingly used in research on quantification of wrist and hand movements [57, 58]. Similarly, the participants will be asked to use their own smartphone microphone to record the speech-like sounds when the ‘dummy’ participant performs the DDK tasks. The audio benchmark for this will be data collected from a high-quality microphone (such as the Blue Yeti USB microphone). For each recording, the distance from the recording device (smartphone and microphone) and the dummy participant will be constrained to about 50 cm to allow for fair comparisons between the devices.

#### Statistical analysis

We will assess the accuracy of the video and audio data collected from each type of smartphone in comparison to the data collected by the wearable sensor measurements and high-quality microphone respectively, using correlation coefficients and mixed effects regression.

The results from this ‘smartphone validation’ study will: (i) allow a correction factor to be introduced, if necessary, into the data analysis later on for a wide range of smartphones and/or, (ii) provide assurance that the data collected for TapTalk on smartphones have little variation across a range of smartphones and in comparison to the movement and audio data collected by the gold -standard wearable sensors and microphone respectively.

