### Setting

Most participants will complete the hand and speech-like movement tests online remotely either at home, or another setting of their choosing, using their own laptop or desktop computer. If they cannot access a computer with a computer camera and microphone, they may attend one of the University of Tasmania research sites to complete the tests on a university laptop. The TAS Test software is an online ‘self-test’ program that guides the participant through a series of screens to collect a range of motor, cognitive and speech tests [38]. It has already successfully collected finger tapping and hand movement data online (as well as various cognitive tests) from ∼1,800 ISLAND Project participants at home and ∼400 participants at University of Tasmania research settings [19, 42]. For the TapTalk project, the TAS Test software will be adapted to collect new finger tapping test data and include an online version of DDK tasks to collect speech-like data.

The full protocol of TAS Test is described in Alty et al.; [38] in brief, when participants log into the TAS Test software, and provide consent online to take part, they are shown an introductory video and general instruction screens. Next, they are asked for permission for the software to switch on their computer camera and microphone. Each individual test (e.g., ‘right hand finger tapping at comfortable pace’ test) within TAS Test has an ‘instruction’ screen followed by a ‘recording’ screen, followed by a “*well done, you have completed the test*” message. To move to the next screen, the participant clicks the ‘next’ button which means the tests are self-paced and participants can take a break at any time. They are shown their progress through TAS Test by green dots on a ‘progress bar’ at the top of the screen; see Fig. 2.

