**Fig. 2 Fig2:**
[figure not shown]
Example of an instruction screen in TAS Test for a finger tapping task [38]. The video instructions are on the left, the text instructions on the right, with the audio icon underneath (so participants can listen to the instructions if preferred). When the participant is ready to attempt the task, they press the ‘Next’ button to move on to the ‘recording’ screen. The green circles above the written instructions show the participant their progress through the various tasks

On each instruction screen, participants will be shown a 5–10 s looped video that demonstrates the hand, or speech-like movement that is required for the task. There are text instructions next to the video and participants may click on an ‘audio’ icon if they would like to hear spoken instructions (the text instructions are read out aloud). When participants are performing the hand or speech-like movements on the ‘recording’ screen, the computer video camera will record the hand movement data and the computer microphone will record the audio data respectively.

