### Extracting hand-speech movement data

We will use deep neural networks and other machine learning methods to develop and train two computer programs that will automatically detect, respectively, hand key points (e.g. finger and thumb tips) in the video data [43], and syllable features in audio recording (Fig. 1). A series of movement features will be extracted in a fixed window period, by (1) experts in hand movement (JA, KL, [name]) and speech-like movements (LG), and (2) deep-learning approach applied directly on processed video data, to analyse their associations with biomarker-defined measures of AD pathology. The processed video data can be the hand-only cropped video or displacement (between fingertip and thumb-tip) over time data extracted from the raw video. Thus, two approaches, expert guided and AI-based ‘deep-learning’, will extract discriminative hand-speech movement features as input data for the multivariable model. The main outcome will be a validated personal computer (laptop and desktop) version of the TapTalk that discriminates preclinical AD from normal ageing in cognitively healthy adults ≥ 50 years old with defined sensitivity and specificity.

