#### Statistical analysis

The data from participants who complete TapTalk on two or more occasions over an 18-month period, and CANTAB on two occasions (2021 and 2023) will be included in the analysis. De-identified ISLAND Project participants will be classified as cognitively ‘stable’ or ‘declining’ using longitudinal CANTAB cognitive scores. TapTalk scores will be calculated using algorithms developed in Study 1. Logistic regression will be used to estimate the odds of a participant being confirmed as ‘declining’ at time T_2_ (24 months) conditioned on TapTalk score at time T_1_ (12 months). The overall outcome of Study 2 will be a smartphone app, TapTalk, that is usable, reliable and validated against established online CANTAB cognitive tests.

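### Study 2.1 benchmarks smartphones against sensors and a microphone, but not against the computers on which the scoring algorithm is trained

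*Protocol article*

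**What the plan says.** All references are to the protocol article.

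- **Training devices.** Under Setting (Aim 1), most participants do the tests remotely "using their own laptop or desktop computer", with a university laptop as the fallback. The text after Fig. 2 adds that "the computer video camera will record the hand movement data and the computer microphone will record the audio data respectively".
- **Product of Study 1.** Under Extracting hand-speech movement data: "The main outcome will be a validated personal computer (laptop and desktop) version of the TapTalk". The Aim 1 Statistical analysis fits the model, tests sensitivity and specificity, and chooses the algorithm, all on these data.
- **Device comparison.** In Study 2.1, participants' phones record one performer "whilst wearing Polhemus movement sensors". For sound, "The audio benchmark for this will be data collected from a high-quality microphone". The analysis assesses phone data "in comparison to the data collected by the wearable sensor measurements and high-quality microphone respectively".
- **Use of that comparison.** The result will "allow a correction factor to be introduced, if necessary, into the data analysis later on for a wide range of smartphones", and/or show that phone data vary little across models and against the two benchmarks.
- **Deployment.** The Study 2.3 Statistical analysis states: "TapTalk scores will be calculated using algorithms developed in Study 1". These are smartphone data. No retraining or recalibration on smartphones is described.

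**The concern.** A model's weights and cut-offs belong to the measurement scale on which they were learned. Here that is the computer camera and microphone. If those devices have their own systematic error, for instance extra apparent timing variability from a low frame rate, smartphone features that match the sensors perfectly would still differ from what the algorithm was trained on. Study 2.1 could not detect this, because no computer is in it.

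This matters because the section Aims and hypothesis promises a smartphone test validated against blood biomarkers. No smartphone study described here has the biomarker as its reference. Study 2.1 records a stand-in performer, Study 2.2 concerns usability and repeatability, Study 2.3 uses CANTAB, and Aim 3 uses MoCA (or RUDAS) and consensus diagnosis. The biomarker evidence comes from computers alone, so extending it to the phone requires that phone and computer scores be equivalent. The plan does not measure that.

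**Working it through.** **1. The device chain.** The plan states no figure for this point, so there is none to reproduce. Set side by side, the steps are:

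| Step | Device | Compared with |
|---|---|---|
| Study 1: train and validate | Computer camera and microphone | p-tau 181 or another blood biomarker |
| Study 2.1: device check | Smartphone | Polhemus sensor, high-quality microphone |
| Study 2.2: reliability | Smartphone at the centre | Smartphone at home |
| Study 2.3: scoring | Smartphone, Study 1 algorithm | CANTAB change |
| Aim 3: scoring | Study smartphone | Clinical diagnosis, MoCA (or RUDAS) |

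No row compares a computer with the sensor, the benchmark microphone or a smartphone.

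**2. Which analyses a mismatch would reach.** Suppose every smartphone score is shifted by the same amount.

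- Study 2.3 regresses decline on the score. The shift changes the intercept, not the odds-ratio slope.
- Aim 3 calculates an AUC, which depends only on ranking and does not change. Its cut-offs are re-estimated with the Youden index, so they absorb the shift.
- A Study 1 cut-off, predicted risk, or sensitivity and specificity quoted for the phone would be wrong.

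If features are distorted unequally, the weights no longer suit the data and the ranking can change too.

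**3. Size for one feature (illustration).** The 60 Hz sensor rate is from Study 2.1. Everything else is assumed: a webcam at 30 frames/s, timing to the nearest frame without interpolation, a true inter-tap SD of 20 ms, a between-person SD of 5 to 8 ms for this feature, normal distributions with equal SD in cases and controls, and a correction that maps phones exactly to the sensor scale.

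- Error SD of an interval = (1000/rate)/√6, the difference of two uniform timing errors.
- Webcam: 33.33/2.449 = 13.6 ms. It reads √(20² + 13.6²) = 24.2 ms.
- Sensor: 16.67/2.449 = 6.8 ms. It reads √(20² + 6.8²) = 21.1 ms.
- Gap, before rounding: 3.06 ms.
- Shift: 3.06/8 = 0.38 SD to 3.06/5 = 0.61 SD, towards less variability, that is, towards a negative result.
- For a cut-off with 80% sensitivity and 80% specificity on webcams, Φ⁻¹(0.80) = 0.842.
- Sensitivity: Φ(0.842 − 0.61) = 59% to Φ(0.842 − 0.38) = 68%.
- Specificity: Φ(0.842 + 0.38) = 89% to Φ(0.842 + 0.61) = 93%.

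**4. Simulation of a two-feature score (illustration).** The simulation used 400,000 people, a prevalence of 17% and a combined AUC of 0.90 (both as in the Aim 1 sample size section), and a cut-off at a predicted risk of 17%. The logistic score was fitted on a distorted webcam scale and applied on the sensor scale. The distortions are assumed.

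| Webcam distortion | Sensitivity | Specificity | AUC on sensor scale |
|---|---|---|---|
| None | 0.82 | 0.82 | 0.90 |
| Offset 0.25 SD, both features | 0.71 | 0.90 | 0.90 |
| Offset 0.5 SD, both features | 0.58 | 0.95 | 0.90 |
| Slope 0.8, both features | 0.86 | 0.77 | 0.90 |
| Slope 0.5, one feature | 0.87 | 0.72 | 0.888 |
| Noise 1 SD, one feature | 0.80 | 0.81 | 0.888 |

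A common offset or slope moves the operating point of a carried-over cut-off and leaves ranking alone. Unequal distortion also costs some AUC, about 0.01 in these cases.

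**The case against.** A reader might infer that the correction aims at the wrong scale, and that shifted cut-offs will spoil Study 2.3 and Aim 3. The text does not support either inference.

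- **The correction.** It is conditional, and its target scale is not stated. Harmonising the phones with each other is an open reading. If computers happen to agree with the benchmarks, there is no bias at all. What remains is that, on either reading, agreement with the training devices is not checked.
- **Studies 2.3 and Aim 3.** Neither is said to use a Study 1 cut-off, and a uniform offset alters neither result. This part of the objection stands in full.
- **The size.** Treating the sensor as error-free would give a shift of (24.2 − 20)/8 to (24.2 − 20)/5, about 0.52 to 0.84 SD, and sensitivity as low as 50%. The stated 60 Hz rate rules that out under the same formula. Even the smaller range concerns one variability feature, while the plan uses a penalised multivariable score.
- **Earlier work.** The article cites laptop-based studies and the full TAS Test protocol, which are not at hand, and says that movement data will be normalised. A computer benchmark may exist there. This article describes none, and it gives no device reference for the normalisation.
- **Detail left to a fuller document.** Device harmonisation often is. Here, however, the article itself fixes the comparator in Study 2.1 and states its purpose.
- **Study 2.2.** It enrols Study 1 participants, so paired computer and smartphone data would exist. The stated analysis correlates smartphone tests only. The data are available, and the analysis that would use them is not described.

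**Conclusion.** The concern holds in a limited form. The algorithm is trained on computer recordings and applied to smartphones, and the only device comparison described omits computers. A correction or assurance from Study 2.1 is therefore tied to a scale not shown to be the training scale.

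The Study 2.3 odds-ratio slope and the Aim 3 AUC and cut-offs are safe from a uniform offset. What is exposed is any Study 1 sensitivity, specificity, cut-off or predicted biomarker risk claimed for the smartphone version, and the score's weighting and ranking where features are distorted unequally.

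The documents do not allow the size to be fixed. The illustrative loss, from 80%/80% to about 59-68% sensitivity and 89-93% specificity, depends on the assumed frame rate, lack of interpolation, inter-tap SD and between-person SD. It shows that a modest device difference could matter, not that one exists.

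**What to change.** 1. In Study 2.1, record the same performances on several typical laptops or desktops, including the university laptops, beside each phone. Add device class to the planned mixed-effects model, with the sensor and the benchmark microphone as common references.
2. In addition or instead, in Study 2.2 compare each participant's Study 1 computer features and score with their smartphone features and score, allowing for the time between them. This is the more direct link, because it uses the participants' own devices.
3. Define any correction as smartphone to Study 1 computer scale, or recalibrate the algorithm on smartphone data.
4. Restate the Study 2.1 outcome so that assurance also requires agreement with the Study 1 device class.

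The cost is modest extra recording in sessions already planned, one more term in a planned model, and one added analysis in Study 2.2. No new participants are needed. A few laptops only approximate the varied home computers of Study 1, which is a reason to do the within-person comparison as well.

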##### Study 2.2

We will undertake a prospective study of 50–100 (randomly selected) ISLAND Project participants who participated in Study 1, own a smartphone, and live within 30 km of the University of Tasmania research centre. They will be invited to attend the University of Tasmania Clinical Research Facility in Hobart for approximately 15 min and asked to bring their own smartphone. Participants will be asked to install the TapTalk app on their own smartphone and complete a consent form. Each participant will then complete the test protocol of hand and speech-like movements in front of the researcher. This will allow the researcher to observe if there are any issues around the usability of installing and operating the TapTalk app.

Each participant will be asked to complete a User Experience Questionnaire immediately after completing both tests, to further evaluate the usability of each form of the test (see supplementary files). We will invite participants to complete TapTalk on a smartphone at least three times at home over the next 7-day period, using the same device each time. They will be sent a reminder email every day over the 7-day period and asked to complete the TapTalk once each day if possible, or at least a minimum of 3 times in total. Their performance on each test will be automatically uploaded to a central secure TapTalk database.

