#### Statistical analysis

The responses to the User Experience Questionnaire, assessing usability, will be analysed with summary statistics. We will examine any practice effects (temporal reliability) by checking for increasing correlation between the first test (in the research centre) and repeated tests (at home) using Kendall rank correlation coefficients. A Kendall rank correlation coefficient of ≥ 0.70 is considered strong; 0.50 to 0.69 as good; 0.30 to 0.49 as moderate and < 0.30 as poor. This will be tested separately for each participant’s device.

The outcome of study 2.2 will be a measure of the usability and reliability of TapTalk. Based on the results from this pilot study, we will make refinements to the software and/or instructions and then invite all ISLAND participants to complete the TapTalk at home as part of study 2.3.

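### Study 2.2 reads practice from a trend in Kendall tau across home repeats without fixing who contributes; if those who do more repeats differ from those who stop at three, the trend can move with no practice

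*Protocol article*

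**What the plan says.** The design is set out under Aim 2, Study 2.2. The sub-study takes 50–100 participants from Study 1. Each does one test in the research centre and is then invited to "complete TapTalk on a smartphone at least three times at home over the next 7-day period". They are "asked to complete the TapTalk once each day if possible, or at least a minimum of 3 times in total". Three home tests is therefore the minimum requested and seven is the daily ideal. The stated support for completion is an email prompt: "They will be sent a reminder email every day over the 7-day period".

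The Statistical analysis paragraph for Study 2.2 says that practice effects, glossed as temporal reliability, will be examined by "checking for increasing correlation between the first test (in the research centre) and repeated tests (at home) using Kendall rank correlation coefficients". Verbal bands follow: "A Kendall rank correlation coefficient of ≥ 0.70 is considered strong; 0.50 to 0.69 as good; 0.30 to 0.49 as moderate", and below 0.30 is poor. One subdivision is stated: "This will be tested separately for each participant’s device". The paragraph does not say that the successive correlations will be computed on the same people.

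**The concern.** Kendall tau between the clinic test and home repeat *k* is a between-person statistic, calculated over the people who supplied repeat *k*. Repeats 1–3 are meant to come from everyone. Repeats 4–7 come from those who did more than the minimum. If those people differ, for instance by being more consistent from one test to the next, tau at the later repeats describes a different group. A change in tau across repeats then mixes a change within people with a change in who is being measured.

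The stated product of Study 2.2 is a measure of usability and reliability, and its results feed refinements to the software and instructions before Study 2.3. A trend caused by the changing set of contributors could be taken for practice. Reliability at later repeats could also look better, or worse, than it is for the whole sample.

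**Working it through.** **Is there a figure to reproduce?** No. The protocol article gives no power calculation, target tau or expected completion rate for Study 2.2. The check is therefore whether the mechanism works and over what range.

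**Inputs from the article.** n = 50–100; 3 to 7 compliant home repeats; trend judged from tau between the clinic test and each home repeat; bands at 0.30, 0.50 and 0.70.

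**Assumptions (not in the article).** Score = stable true value (SD 1) + independent error. There is no practice effect unless stated. Except where noted, repeats per person are spread evenly over 3–7, so the share contributing is 100% at repeats 1–3, then 80%, 60%, 40% and 20% at repeats 4–7. At n = 50 that is 50, 40, 30, 20 and 10 people; at n = 100 it is 100, 80, 60, 40 and 20.

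**Why tau depends on who contributes.** For normal scores with error SD s, the correlation between two tests is r = 1/(1 + s²), and tau = (2/π)·arcsin(r).
- s = 0.6: r = 1/1.36 = 0.735, tau = 0.53.
- s = 0.4: r = 1/1.16 = 0.862, tau = 0.66.

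A group with smaller error has a higher tau at every repeat, whether or not anyone has improved.

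**Simulated mean tau.** All rows have zero practice except the last.

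| Assumed pattern | n | Repeat 1 | Repeat 7 | Share of studies with tau at repeat 7 above repeat 1 |
|---|---|---|---|---|
| Everyone completes all seven | 50 / 100 | 0.52 / 0.52 | 0.53 / 0.53 | 0.52 / 0.51 |
| 3–7 repeats, unrelated to performance | 50 / 100 | 0.53 / 0.52 | 0.53 / 0.52 | 0.55 / 0.51 |
| Weak link: error SD 0.7 (3 tests) to 0.6 (7 tests) | 75 | 0.49 | 0.53 | about 0.61 |
| Moderate link: log error SD falls 0.25 per SD of keenness | 50 / 100 | 0.51 / 0.52 | 0.64 / 0.64 | 0.79 / 0.89 |
| Strong link: error SD 0.9 to 0.4 | 75 | 0.49–0.50 | 0.66 | 0.90 |
| Strong link: log error SD falls 0.5 per SD of keenness | 50 / 100 | 0.48 / 0.48 | 0.72 / 0.73 | 0.94 / 0.99 |
| Completion linked to score level only | 50 / 100 | 0.53 / 0.53 | 0.50 / 0.48 | 0.47 / 0.38 |
| Real gain of 0.3 SD per repeat, everyone completes seven | 50 / 100 | 0.53 / 0.53 | 0.53 / 0.53 | not computed |

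**Effect of better completion.** If 70% of 75 participants complete all seven, the strong link (0.9 to 0.4) gives about 0.60 to 0.67, and the weak link (0.7 to 0.6) about 0.52 to 0.53. The artefact shrinks as completion rises.

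**Precision.** Even when completion is unrelated to performance, the SD of tau grows from 0.07 at repeat 1 to 0.18 at repeat 7 (n = 50), and from 0.05 to 0.12 (n = 100).

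**Same people throughout.** In the steeper strong-link pattern, tau restricted to home tests 1–3 in all participants is 0.48, 0.48, 0.48 (n = 50) and 0.48, 0.48, 0.49 (n = 100). Tau at repeat 3 exceeds tau at repeat 1 in about half of studies, as it should with no trend.

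**A limit of tau itself.** In the last row everyone improves by 0.3 SD at each repeat with complete data, and tau does not move. Adding the same amount to everyone's score leaves the ranks unchanged.

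**The case against.** **Analysis-set detail belongs elsewhere.** A journal article condenses the plan, and a full protocol or analysis plan could name a common set. That is fair as far as the missing detail goes. But the article itself fixes the estimator, the comparison across repeats and the bands, and pairs them with a number of repeats that each participant chooses. Followed as written, each tau may come from different people.

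**The shrinking, keener group is assumed.** This stands. A reader might infer that later repeats will come from a dwindling set of more able users and that tau will therefore rise. The article does not support that. It asks for a test every day, sends a reminder every day and gives no completion rate. Near-full completion is possible, and the set of contributors would then barely change. The direction is not fixed either: selection on score level lowers tau, and completion unrelated to performance costs only precision.

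**The simulation pools devices.** This also stands. The article tests by device and the simulation does not. Splitting by device makes later cells smaller still: 20% of 75 is 15 people at repeat 7 before any split. The smooth pooled trends above show the mechanism; they do not forecast what Study 2.2 will display.

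**Little depends on it.** Study 2.2 is described as a pilot that leads to refinements. No go/no-go rule or confirmatory claim rests on the trend, and the bands are descriptive. This keeps the point minor.

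**Conclusion.** The point holds in conditional form. Because 3 to 7 home repeats are all compliant and the trend in tau is not tied to a fixed set of people, the trend can move with no practice if those who do more repeats differ from those who stop at three. Under the stated assumptions the change from repeat 1 to repeat 7 runs from a small fall (0.53 to 0.48–0.50), through none, to a small rise (0.49 to 0.53) or a large one (about 0.48–0.50 to 0.66–0.73). The top of that range crosses from the article's moderate band into its strong band. Which of these applies cannot be known from the article.

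Separately, and whatever the completion pattern, a rising rank correlation is a poor sign of practice, since a uniform gain leaves it flat. Shortening the tau trend to fewer repeats would remove the selection artefact but would not turn tau into a measure of practice. The importance is minor: a pilot sub-study with a cheap remedy.

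**What to change.** In the Statistical analysis paragraph for Study 2.2:

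1. Compare tau across repeats only within one fixed set of participants, for example home tests 1–3 in all who completed them.
2. Report the number of participants contributing at each repeat.
3. Assess practice with all repeats in a within-person mixed model of the score on test number, with participant random effects. Keep tau as a description of reliability.

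The cost is a few sentences and a little more analysis work, with no new data. The downside is that later repeats do not enter the tau comparison, although they still inform the mixed model.
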